#### Further parameters

##### Duration of consultations

We will assess the duration of decision coaching sessions and physician encounters and the interval between the encounters.

In addition, data from all participants will be collected during the accompanying process evaluation.

### Procedures and data collection

#### Identification of eligible patients

Potentially eligible women will be identified during the tumor boards or by upcoming appointments. To avoid selection bias, an independent person will contact participating breast care centers (specialized nurses) weekly after the tumor boards to identify eligible patients. Nurses will be instructed to alert physicians of eligible patients. The number of primary cases within the study period will be compared to the number of patients identified as eligible and asked to participate. Physicians of the participating breast care centers will fill in a recruitment form. If inclusion criteria are met, women will be invited to participate in the study, and their informed consent will be obtained (see Fig. 1). To avoid recruitment bias, physicians receive a guideline to invite women with DCIS in a standardized manner. Reasons to decline study participation will be documented if unveiled.

#### Baseline data and allocation

Women in the IG will fill in the baseline data and attitude toward treatment. Completion of questionnaires will require 5 min. Afterward, women receive the DCIS-ptDA and the patient decision guidance.

For women in the CG, the physician encounter will be interrupted and women are invited to fill in baseline data forms. Women are given enough time to think about study participation. If they decide to participate, the patient-physician encounter will continue according to the study protocol.

#### Encounters one and two

Multiple assessments of the decisional conflict scale and the MAPPIN-Q_patient_ can influence the results. Similar preconditions between professionals and women, as well as between the IG and CG, may avoid this bias. Therefore, women receive these questionnaires for reading before the encounters with nurses and physicians. Before the coaching session (and after reading of the ptDA), the patient’s attitude toward treatment options will be assessed again. The reading and completion of questionnaires will require 5 min. After the last decision coaching session, patients in the IG will complete the MAPPIN-Q_patient_, the DCS and the attitude scale. Completion will require about 10 min.

Patients in the IG will complete the remaining questionnaires, including the risk knowledge test after the final physician encounter, which requires about 15 min.

In the CG, patients will complete MAPPIN-Q_patient_, the attitude towards decision questionnaire, the DCS and the risk knowledge questionnaire after finishing the physician encounter (15 min).

After the final encounter with patients, nurses in the IG and physicians in IG and CG will fill in the MAPPIN-Q_physician/nurse_ and the DCS, respectively (5 min).

Women will complete all questionnaires during their appointments in the breast care centers to ensure completeness. If necessary, women will be provided with a prepaid envelope.

If women do not complete all forms, they will be contacted by the study nurse via telephone. Women will be asked to fill in the forms at their next appointment. If the decision-making process was already completed, missing forms will be send to the woman by post.

We do not expect women to miss an appointment because often women feel time pressure for decision-making due to the threatening diagnosis. Women would be contacted by decision coaches to arrange a new appointment if they missed one.

All encounters will be video recorded by nurses and physicians. The video camera will not focus on patients but on the desk with the coaching material. The recordings will be rated independently with the MAPPIN-O_dyad_by two raters. Discrepancies will be solved by discussion after finishing the rating respectively.

The final choice of women will be assessed 2 months after the treatment decision was made.

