**Fig. 1 Fig1:**
[figure not shown]
Participant timeline

Nurses will provide information on the **decision coaching,** the **evidence-based ptDA** and the decision guidance that is targeted to the decision to be made. They will also arrange a new appointment within 1 week for the decision coaching and provide her contact details. At the next appointment, the nurse supports the woman’s decision-making process in a structured manner, considering the six steps of SDM [61, 62]:Definition of the problem requiring a decision-making processKey message (There is more than one option, and the best option depends on how the patients value the evidence, the benefits and harms considering their expectations and preferences.)Information about the options, including benefits and harms based on EBPIClarifying patient’s values and preferencesDecision-making (optional to postpone the decision)Arrangement

Nurses will carry out the first five steps. If the woman is not ready to make a decision yet, an additional decision coaching session will be offered. If the woman makes her decision, the nurse will arrange the physician consultation in which physician and woman discuss the preferred option and talk about remaining questions. Patients and physicians will make an arrangement about treatment or watchful waiting (sixth SDM-step) and possibilities to evaluate the decision. Women are allowed to revise their decision at any time if they are not satisfied with their initial decision.

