#### Control cluster

In the control cluster, standard care will be delivered. Women will not receive any additional information or counselling on treatment options other than that usually provided by breast care centers. In general, standard care comprises one or two physician encounters in which the women are informed about their diagnosis and the treatment recommendation of the tumor board and their informed consent for treatment is obtained. Standard care procedures of each breast care center will be assessed at the beginning of the study. We expect centers to be comparable due to certification guidelines.

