The single dimensions of the instrument are described below:Risk knowledgeA 12-item knowledge test has been developed to measure risk knowledge. The test includes questions on diagnosis and prognosis of DCIS and benefits and harms of available treatment options in multiple-choice format. It was pretested in the pilot trial. However, it cannot be considered a validated scale. The score is calculated by the sum of correct answers (maximum value 12). Total values will be dichotomized in adequate risk knowledge (at least 75 %; ≥ 8 correct answers) and non-adequate knowledge (<8 correct answers). If patients fill in at least one item of the risk knowledge test, unanswered questions will be rated as incorrect. If none of the questions is answered, the test will be classified as missing data. All patients will fill in the risk knowledge test after their last physician encounter to avoid questions from patients triggered from the test items.AttitudeThe attitude of patients toward the options will be assessed during the SDM process. Because the decision can be influenced by several factors, the attitude in the IG will be assessed at baseline, before the first decision coaching session (after reading the decision aid), after the last decision coaching session and after the final physician encounter in which the treatment decision is made. In the CG, attitude will be assessed before (baseline) and after the physician encounter. The questionnaire comprises the attitude for every option using a four-point Likert scale (“non-sensible” to “sensible”). We will only include the score regarding the treatment option that was finally chosen by patients in the measure of informed choice. The further judgments will be assessed in the scope of the process evaluation. The scale is newly developed.UptakeUptake indicates whether women stick to their decisions made with the medical team (nurses and physicians) within the decision-making process. This information will be extracted from patient records 2 months after the final physician encounter and is included in the measure of informed choice.

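### The risk knowledge test may be completed at home, where only intervention women have been given the decision aid, so looked-up answers could inflate informed choice in that arm

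*Protocol article*

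**What the plan says.** All references are to the protocol article.

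- **Place of completion** (Encounters one and two). The default is the centre: "Women will complete all questionnaires during their appointments in the breast care centers to ensure completeness". Two exceptions follow: "If necessary, women will be provided with a prepaid envelope", and, after a reminder call from the study nurse, "If the decision-making process was already completed, missing forms will be send to the woman by post". No form is exempted from either.
- **Timing of the test** (Informed choice, risk knowledge). "All patients will fill in the risk knowledge test after their last physician encounter to avoid questions from patients triggered from the test items". This applies to both arms.
- **Who holds the decision aid.** In the intervention group (IG), once baseline forms are done: "Afterward, women receive the DCIS-ptDA and the patient decision guidance" (Baseline data and allocation). Time to read it follows, since nurses set the coaching session for later: "They will also arrange a new appointment within 1 week for the decision coaching" (Interventions, Patients). For the control group (CG): "Women will not receive any additional information or counselling on treatment options other than that usually provided by breast care centers" (Control cluster).
- **Content.** The aid describes DCIS, how it develops untreated, and the advantages and drawbacks of each option (Evidence based ptDA). The 12 multiple-choice items cover diagnosis, prognosis and the same advantages and drawbacks (Informed choice).
- **Use.** Adequate knowledge, together with a positive attitude to the chosen option, defines an informed choice. Knowledge is also analysed on its own. Secondary outcomes are analysed as complete cases (Handling of missing data).

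**The concern.** The knowledge component should show what a woman knew when the decision was made. Knowledge gained from reading the aid is the intended effect of the intervention. An answer looked up while filling in the form is not, and a form completed unsupervised at home cannot tell the two apart. The source most useful for looking up has been supplied to one arm only, so any such error would tend to favour the IG.

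More informed choices is the second hypothesis under Objectives, and adequate knowledge is a necessary condition for that outcome. The score is also cut into adequate and inadequate, so a few looked-up answers can move a woman across the line. The cluster-adjusted chi-square test and the complete-case rule do not address where the form was filled in. The same section wants similar preconditions in the two arms for repeated questionnaires, and the unrestricted postal rule sits badly with that aim.

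**Working it through.** **1. Does the postal rule reach the knowledge test?** The test comes after the last physician encounter, when the decision process is normally complete. Completing a missing form at the next appointment is then rarely possible, so post is the prescribed route for an outstanding test.

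**2. Is there a figure in the plan to reproduce?** None concerns this point: neither a home-completion share nor an expected informed-choice rate is given. The sample size does reproduce. With a difference of 0.25, SD 0.4, two-sided alpha 0.05 and 90% power, 53.8 women per arm are needed. The design effect is 1 + (12 − 1) × 0.02 = 1.22, and 53.8 × 1.22 = 65.6 per arm, or 65.6 / 12 = 5.47 clusters, rounded up to 6. One further cluster per arm gives 7, hence 14 centres and 168 women. A non-central t check with 2(k − 1) degrees of freedom gives power 0.863 with 6 clusters per arm and 0.919 with 7. The calculation rests on MAPPIN-O dyad only, so home-completed knowledge tests do not touch it.

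**3. Added IG difference in informed choice when there is no true effect.**

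Δ = f × (1 − p) × c

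- f: share of IG tests done at home (assumed)
- p: informed-choice rate under supervised testing (assumed, equal in both arms)
- c: share of otherwise uninformed home completers who become informed by looking up (assumed)
- No look-up gain in the CG (assumed)

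Example, middle setting at f = 10%: 0.10 × 0.60 × 0.50 = 0.030, or 3.0 points.

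**4. Chance of a falsely significant result.** Normal approximation, with 192 / 2 = 96 women per arm. The design effect from the primary outcome is borrowed as an assumption: n = 96 / 1.22 = 78.7.

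SE = √{[(p + Δ)(1 − p − Δ) + p(1 − p)] / n}, s = Δ / SE, chance = 1 − Φ(1.96 − s) + Φ(−1.96 − s)

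Same example: SE = √[(0.43 × 0.57 + 0.40 × 0.60) / 78.7] = 0.0785; s = 0.030 / 0.0785 = 0.38; chance = 6.7% against a nominal 5%.

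| f | Low: p = 0.6, c = 0.25 | Middle: p = 0.4, c = 0.5 | High: p = 0.2, c = 1.0 |
|---|---|---|---|
| 5% | +0.5 points; 5.0% | +1.5 points; 5.4% | +4.0 points; 9.3% |
| 10% | +1.0; 5.2% | +3.0; 6.7% | +8.0; 21.9% |
| 20% | +2.0; 5.8% | +6.0; 11.9% | +16.0; 62.2% |
| 30% | +3.0; 6.7% | +9.0; 20.7% | +24.0; 91.6% |

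The high column is a ceiling. It needs every otherwise uninformed home completer to look up enough answers and also to hold a positive attitude to her chosen option.

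**5. If no home-completed test entered the comparison**, f = 0 and Δ = 0.

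**The case against.** The strongest reply is that home completion is a fallback. The centre is the rule, the envelope is for cases of need, and a missing form prompts a telephone call before anything is posted. Under Handling of missing data the authors do not expect missing values. If that holds, f is a few per cent and the effect is negligible in all but the ceiling column. This stands, and it limits the size of the point.

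Three stronger readings are tempting, and the documents support none of them.

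- A reader might infer that informed choice will be inflated. No home-completion rate is given. The text shows overlap of topics, not that the aid answers each item, that it is still at hand, or that women would consult it during the test. CG women could look elsewhere, which would offset part of the difference.
- A reader might take a shift in adequate knowledge as the shift in informed choice. If, for illustration, 50% were adequate under supervision and 90% with the aid open, knowledge would move by 0.40 × f: 2, 4 or 8 points at 5%, 10% or 20%. Informed choice also needs a positive attitude, which looking up does not supply.
- A reader might infer that late decisional conflict or attitude forms bias the comparison too. IG forms can also be posted late, so no direction can be shown.

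Finally, the article is condensed. Form fields, test instructions and sensitivity analyses may sit in the full protocol or analysis plan, and their absence here is no fault. What remains is a rule that the article does state: it sends missing forms home without exempting the knowledge test.

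**Conclusion.** The point holds as a possible bias in a secondary outcome. The home route is written into the protocol, it reaches the knowledge test, and only the IG has been given material on the tested topics, so looked-up answers could inflate adequate knowledge and hence informed choice in that arm.

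Its size cannot be fixed from the documents. Under the assumed inputs it is about 0.5 to 4 points on informed choice at 5% home completion. It becomes material at roughly 10–20% or more in the middle and high settings, and stays small throughout in the low setting. These figures assume no look-up gain in the CG, equal true rates in both arms, full recruitment and a borrowed ICC of 0.02. The primary outcome and the sample size are not affected. A change is still worthwhile because it is cheap, and the place of completion cannot be recovered later if it is not recorded.

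**What to change.** In Encounters one and two, take the risk knowledge test out of the general envelope and postal rule. It should be completed in the centre directly after the final physician encounter, without written material, in both arms. Post should remain only as a last resort, with a printed instruction to answer without the decision aid or other sources.

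Record the place and date of completion on the form. Repeat the informed-choice and knowledge comparisons without home-completed tests as a sensitivity analysis. Setting all such tests to missing in the main analysis is not advised: under the complete-case rule it could remove a selected group of women, possibly a different one in each arm.

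The cost is a change of wording, two form fields, one extra analysis and a slightly smaller sample in that analysis. A closed-book instruction at home cannot be enforced, which is why the sensitivity analysis is still needed.

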### Sample size

The sample size calculation is adapted to the primary outcome (MAPPIN-O_dyad_) and is conducted under the assumption of the same variances in both groups for a continuous normally distributed target variable of a two-arm cluster randomized controlled trial.

The assumption on the expected difference between IG and KG and the possible size of the cluster effect is based on previous research [77, 79–81]. A difference of 0.25 in the primary outcome should be revealed between the groups with a power of 90 % and an assumed standard deviation of 0.4. Because we could not identify reliable estimates of the intracluster correlation coefficient (ICCC), we estimate an intracluster correlation coefficient of 0.02 based on previous studies in stroke units and hospitals and due to the fact that breast care centers feature a high standardized care process through the certification [79, 80]. The cluster size will be m = 12 (12 patients per breast care center). As a primary test, a cluster-adjusted t-test according to Donner et al. [82] will be used. The calculation results in a sample size of 14 breast care centers with 168 patients based on an alpha of 0.05. Under consideration of drop-outs, 16 breast care centers will be recruited with a total sample size of n = 192 patients.

### Recruitment

Breast care centers that have at least 20 primary cases of DCIS per year will be invited for study participation. Breast care centers and potential participating health care professionals will be informed about the study. Each breast care center will recruit 12 patients within 9 months.

The recruitment of women will be conducted by the physicians of the breast care centers.

### Allocation

The statistician (BH) has provided a computer-generated allocation sequence. A random permuted block design using blocks of sizes 4, 6 or 8 will be used. No stratification is performed. An independent external person will unveil the allocation after inclusion of all breast care centers. Corresponding to the cluster design, breast care centers will be aware of their allocation status. To avoid selection bias, patients will not receive information about their allocation status. Women will be asked to assume which kind of counselling procedure they received because the unveiling of allocation could have influenced their responses.

If patients would have information about their allocation status before participation, they might not agree to participate or a nocebo-effect might occur in the CG due to the assumption that their treatment might be inferior to the IG. As opposed to this, patients in the intervention group might not agree since they estimate for example, the expenditure of time too high or they would insist on immediate treatment decisions by physicians.

### Blinding

Clusters and patients cannot be blinded (see above). Due to the obviousness of the material used in the IG (for example, prompt cards, decision guidance and fact sheets), video raters cannot be blinded. However, the members of the research team who enter the data are blinded to allocation. The analyst will conduct a blinded review of data before the study groups are unveiled, and the final statistical analysis will be conducted.

### Data management

Data will be administered and entered by the team members of the Unit of Health Sciences and Education of the University of Hamburg. Each study participant will receive a pseudonym to allow for combining of data sets of different time points. Data entry will be verified by two blinded members of the research team. Data will be stored for 10 years as suggested by the German Research Foundation (DFG) [83].

### Statistical methods

#### Statistical methods for analysing primary and secondary outcomes

Data analysis will be conducted following the intention-to-treat principle.

The patient participation (MAPPIN’SDM) in the decision process will be estimated by the primary outcome. Mean values and cluster-adjusted standard deviation [82] in IG and CG will be estimated and compared with a cluster-adjusted t-test. Cluster adjustment is performed using the intracluster correlation coefficient as described in detail by Donner et al. [82]. Linear mixed models including clusters as random effect would be an alternative model [82]. Using a simple design, as in this trial, similar results would be expected for both methods [82]. We decided to use the simpler method of a cluster-adjusted t-test, which has been used in many other cluster randomized controlled trials before.

For all further MAPPIN-questionnaires (secondary outcome) and ratings (inclusively concordance), cluster-adjusted t-tests are also used under the same assumption as described before.

Sub-analysis will be conducted for physician and nurse encounters separately for example, if some of the indicators of MAPPIN could be observed more frequently in nurse or in physician encounters.

Likelihoods of informed choices will be estimated by cluster-adjusted confidence intervals and compared by a cluster-adjusted chi-square-test [82].

Additionally, as secondary analysis, the risk knowledge will be compared nonparametrically between the IG and CG by a Wilcoxon-test on cluster-level (as a non-dichotomized measure).

As secondary analysis decisional conflict (DCS) will be compared by a cluster-adjusted t-test.

All tests will be carried out two-tailed with a significance level of α = 0.05, confidence intervals will be calculated as two-tailed 95 % confidence intervals.

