#### Pilot trial

Each component of the intervention was separately piloted [54]. Finally, feasibility and acceptability of the complete program has been evaluated in a phase II study [53].

Two breast care centers (four nurses and five physicians) in Berlin, Germany, recruited up to 6 patients with DCIS [53]. All encounters with patients and nurses were videotaped and analyzed. In sum, the study showed that the program is feasible and acceptable. However, we also identified barriers. The physician workshop revealed the physicians’ desire to discuss treatment options; in standard care, usually only the recommendation of the tumor board is communicated to the patient, which is in line with medical guidelines. This option is often seen as the only possible treatment. Therefore, an open decision-making process is inhibited. Physicians also unveiled patients’ supposed expectation of doctors. According to their opinions, patients expect clear treatment recommendations. Both professional groups - nurses and physicians - pointed out that it is not necessary to ask patients for their preferences because they already know which option would be the best for the patients. Although each woman fulfilling the inclusion criteria should have been asked for study participation, not all women were asked for participation because physicians were concerned that some women might be overburdened by SDM due to age or educational background. Another barrier consists in the predefined number of specific surgical procedures that lead to a doubtful incentive for breast care centers. Physicians were concerned about offering women all treatment options since they had to justify their treatment to the certification body that defines the quality indicators.

We address the potential barriers in our educational intervention by discussing the possible impact of personal attitudes and giving advice on how to communicate the recommendation of the tumor board. In addition, we developed supplementary material such as prompt cards and fact sheets to structure the decision coaching sessions.

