### Baseline data

The following data will be surveyed from breast care centers before randomization: Primary cases of DCIS treated with (1) breast-conserving therapy, (2) additional recommendation of radiotherapy afterwards and (3) mastectomy in 2014, certification body (Onkozert, EUSOMA, ÄKzert), number of specialized nurses in the breast care centers, number of treating physicians and procedures in the breast care center.

Baseline characteristics of specialized nurses include age, gender, working experience, training and education, job specification, knowledge about DCIS, experiences in patient counselling, participation in physician consultations and tumor boards and nurses’ understanding of their role.

Baseline characteristics of physicians include age, gender, working experience in senology, qualification, attitude towards the inter-professional collaboration and knowledge about evidence-based medicine and SDM.

Baseline characteristics of women with DCIS include age, educational level, disease and diagnostic parameters (size of DCIS, histologic type = grading, architecture, focality, hormone-/HER2-receptor-status if available, comorbidities, mode of detection) (all diagnostic parameters will be extracted from the patient record), information about health information behavior, and advance information about DCIS.

All baseline characteristics except for the women will be assessed before randomization to avoid bias.

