#### Methods for any additional analyses

Baseline data of both groups will be analyzed descriptively. To ensure test quality, the used instruments will be checked by item analysis that is oriented on the common parameters in literature [84].

Furthermore, it will be assessed descriptively, whether women in the IG choose less invasive treatments more often compared to women in the CG.

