## Discussion

The study aims at the evaluation of a structure changing complex intervention to improve informed SDM in breast care centers. As yet, decision coaches have not been implemented in standard care in oncology in the German healthcare system. An environmental scan of Légaré et al. [90] reveals that inter-professional approaches of shared decision-making are lacking. The intervention has advantages such as the low-threshold offer for patients and continuity of care. The strength of the study is that our outcome focuses on the mutual SDM behavior of all involved parties. However, we could not take into account the perceived SDM behavior of the involved parties in our primary outcome, since no validated compound measure for inter-professional SDM exists.

Our primary endpoint assesses the extent of SDM of the whole decision-making processes. Each process is based on two talks in the IG and one talk in the CG due to our structural intervention. Talking with two health care professionals may result in higher overall SDM performance. Hence, systematic differences in this outcome are possible. In the IG, the decision-making process is split. In this respect, focusing only one talk would skip part of the whole process. Applying one holistic measurement for the process in the IG will meet this doubt.

In addition, using MAPPIN’SDM for decision-making processes comprising two talks has not been validated yet. To estimate construct validity, interrater reliabilities will be computed and the consensus ratings of two independent raters will be used to calculate the primary endpoint.

The study has limitations, since blinding of clusters, women and assessors is not possible. Since the allocation of women is not concealed, a selection or participation bias may occur.

The potential selection bias of participating women is challenging. Physicians might not ask every eligible woman, because of implicit assumptions of eligibility for example, age or educational background. This issue will be discussed with all participating physicians. The number of eligible women will be monitored in all centers. In addition, strategies to speak to eligible women will be discussed and a guideline for physicians will be provided.

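### The primary comparison takes no patient covariates, although physicians who know their centre's arm recruit after allocation and the protocol itself names age and education as possible grounds for selection

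*Protocol article*

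**What the plan says.** **Analysis.** Under Statistical methods for analysing primary and secondary outcomes, the protocol article compares the arms on MAPPIN-O dyad with a t-test corrected for clustering through the intracluster correlation. It mentions a second method, "Linear mixed models including clusters as random effect would be an alternative model", and sets it aside: "Using a simple design, as in this trial, similar results would be expected for both methods". It then settles the matter: "We decided to use the simpler method of a cluster-adjusted t-test, which has been used in many other cluster randomized controlled trials before". No patient covariate enters either method as described. Under Methods for any additional analyses, "Baseline data of both groups will be analyzed descriptively". The only sensitivity analysis stated for the primary outcome (Handling of missing data) concerns imputed values.

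**Recruitment.** Under Allocation, the allocation is disclosed once all centres are included, and centres know their arm. Under Recruitment, "The recruitment of women will be conducted by the physicians of the breast care centers".

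**Selection.** The Discussion concedes that selection or participation bias may occur because the allocation of women is not concealed, and adds: "Physicians might not ask every eligible woman, because of implicit assumptions of eligibility for example, age or educational background". The Pilot trial section reports that not all eligible women were asked, because "physicians were concerned that some women might be overburdened by SDM due to age or educational background".

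**Data.** "Baseline characteristics of women with DCIS include age, educational level, disease and diagnostic parameters" (Baseline data).

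**Safeguards.** Under Identification of eligible patients: weekly contact by an independent person, nurses alerting physicians, a standardised invitation guideline, and comparison of primary cases with women identified and asked. Patients are not told their arm (Allocation). The Discussion adds talks with participating physicians and monitoring of eligible numbers.

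**The concern.** Randomising centres makes the centres comparable in expectation. It does not make the enrolled women comparable when those who invite them know the arm. If the factors guiding invitation differ between arms and also predict how much shared decision-making an observer sees, the unadjusted difference mixes case mix with the effect of the program.

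A difference by arm is plausible. The worry reported in the pilot was burden from shared decision-making, and women in intervention centres are the ones offered the decision aid and coaching. The protocol names two possible selection factors and plans to measure both, but uses neither in any comparative analysis it states. The safeguards can limit selection or show how much occurred; they do not correct the estimate.

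At stake are the size of the estimated effect and, if the imbalance is large enough, the type I error or power of the primary test.

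**Working it through.** **1. The plan's own figure.** Inputs from Sample size: difference 0.25, SD 0.4, two-sided alpha 0.05, power 90%, ICC 0.02, 12 women per centre.

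- Without clustering: 2 × (0.4 × (1.960 + 1.282) / 0.25)² = 53.8 women per arm.
- Design effect: 1 + 11 × 0.02 = 1.22. 53.8 × 1.22 = 65.6 women, or 65.6 / 12 = 5.47, so 6 centres per arm.
- One extra centre per arm for the small number of clusters gives 7 per arm: 14 centres and 168 women, as stated.
- Noncentral t check (2k − 2 degrees of freedom, k centres per arm): 86.3% power with 12 centres, 91.9% with 14, 95.4% with 16.

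The sample size is not in error.

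**2. Bias without adjustment.** Let ρ be the correlation of the covariate with the outcome and g the arm difference in the covariate, in SD units. The documents give neither. The assumed ranges are ρ = 0.1 to 0.4 and g = 0.25 to 0.75.

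- Bias = ρ × 0.4 × g. Lowest: 0.1 × 0.4 × 0.25 = 0.01. Highest: 0.4 × 0.4 × 0.75 = 0.12.
- Standard error with 16 centres: 0.4 × √(2 × 1.22 / 96) = 0.0638.
- Type I error: noncentral t, 14 degrees of freedom, noncentrality bias / 0.0638.
- Power if the imbalance works against the program: noncentrality (0.25 − bias) / 0.0638.
- Approximate adjusted power: standard error multiplied by √(1 − ρ²) × √(1 + g²/4).

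| ρ | g | Bias | Share of 0.25 | Type I error, unadjusted | Power if imbalance is adverse, unadjusted | Adjusted power |
|---|---|---|---|---|---|---|
| 0.1 | 0.25 | 0.01 | 4% | 5.2% | 93.8% | 95.3% |
| 0.2 | 0.5 | 0.04 | 16% | 9.0% | 86.4% | 95.0% |
| 0.3 | 0.5 | 0.06 | 24% | 14.2% | 79.1% | 95.9% |
| 0.4 | 0.5 | 0.08 | 32% | 21.6% | 69.8% | 97.1% |
| 0.4 | 0.75 | 0.12 | 48% | 41.8% | 47.5% | 96.1% |

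Over the whole grid, adjusted power at 16 centres is about 93% to 98%.

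**3. Simulation check.** 16 centres of 12, ICC 0.02, 4,000 runs per scenario. The adjusted version estimates the covariate slope with arm in the model, then runs a t-test on adjusted centre means.

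- No true effect, g = 0.5, ρ = 0.2, 0.3 and 0.4: unadjusted type I error 9.1%, 14.2% and 22.5%; adjusted 6.1%, 5.6% and 5.5%, with adjusted bias about 0.
- True effect 0.25, ρ = 0.3, imbalance of 0.5 SD against the program: power 79.5% unadjusted, 96.5% adjusted.

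The adjusted error rates sit slightly above 5%. This simple version ignores uncertainty in the estimated slope, so the final method should allow for it.

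**4. Precision.** Suppose age and education explain 10% to 20% of the variance (an assumption).

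- Explained equally between and within centres: the standard error is multiplied by √0.9 = 0.949 or √0.8 = 0.894, a fall of about 5% to 11%.
- Explained within centres only: the variance of a centre mean is proportional to 0.02 + 0.98/12 = 0.1017. It falls to 0.02 + 0.88/12 = 0.0933 or 0.02 + 0.78/12 = 0.0850. The square roots of the ratios are 0.958 and 0.914, a fall of about 4% to 9%.

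Arm imbalance in the covariates takes back part of this gain.

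**The case against.** **Selection by arm is not shown.** A reader might infer that selection will differ between arms. The documents do not support that. The pilot had two centres, up to 6 patients and no control arm; the Discussion says only that physicians might leave women out and does not distinguish arms. The pilot barriers are also addressed in the educational intervention, which only intervention centres receive, so a difference could shrink or reverse. Selection that is equal in both arms would not bias the contrast. This stands, and the point is about what may happen.

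**Safeguards exist.** They are real and fairly extensive. Room to select is also limited in the smallest centres: 20 cases a year is about 15 in 9 months, for 12 places. Larger centres have more room. This lowers the likely size of the bias but does not supply an analytic remedy.

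**The argument for the t-test is sound as far as it goes.** A reader might infer that the claimed similarity of the two methods is wrong. It is not: without covariates, both estimate nearly the same difference, and imbalance would bias both alike. The statement simply does not address recruitment after allocation. Nor does the mixed model, as the protocol describes it, contain covariates.

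**An adjusted sensitivity analysis may be in an analysis plan that is not shown.** That is possible. But the protocol itself fixes the covariate-free primary test and argues for it, so the choice is open to comment.

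**Power is adequate.** Also true, at 95.4% with 16 centres. Precision is a side benefit, not the reason for the change.

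**Conclusion.** The concern holds in limited form. The cluster-adjusted t-test is a valid and adequately powered test if the women enrolled are comparable between arms. The plan has no analytic protection if they are not, on two factors that it names itself and intends to record.

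The size is unknown. Under the assumed ranges the bias runs from 0.01 to 0.12 (4% to 48% of the target), and the type I error at 16 centres from 5.2% to about 42%. No single value in that range should be read as an expectation. For example, take 40% against 20% of women with low education and a score 0.3 lower in that group: the bias is 0.20 × 0.3 = 0.06. But a 0.3 deficit is 0.75 SD and exceeds the target effect itself. With a pooled proportion of 30% it implies a correlation of 0.3 × √(0.3 × 0.7) / 0.4 = 0.34, toward the top of the range.

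A reader might also infer that adjustment would remove selection bias. It would not: the protocol gives age and education only as examples, and selection on unmeasured factors would remain. Adjusting for these two is legitimate even though women's baseline data are collected after randomisation, because the program cannot change either.

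**What to change.** In the statistical methods section, before the analyst is unblinded, pre-specify an analysis of MAPPIN-O dyad adjusted for age and educational level.

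- **Model:** a linear mixed model with arm, age and educational level as fixed effects, centre as random intercept and small-sample degrees of freedom (for example Kenward-Roger). An equivalent two-stage analysis on centre-level adjusted means would also serve; it should keep arm in the first stage and allow for the estimated slopes.
- **Status:** preferably primary, with the cluster-adjusted t-test as supportive analysis. At minimum, a key sensitivity analysis.
- **Other outcomes:** the same covariates for the decisional conflict scale, and for informed choice with a model suited to a binary outcome in clustered data.
- **Statement of limits:** say that adjustment reduces bias from these two measured factors only, and that the expected gain in standard error is modest (about 4% to 11% if they explain 10% to 20% of the variance).

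**Cost:** a change to the protocol text, since the protocol fixes the present test, plus slightly more analysis work and a few degrees of freedom. No extra patients are needed, and both covariates are already planned for collection.
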